### 4.3 Treatment Phase

#### Study visit procedures

Study visits will occur at weeks 2, 4, 8, 12, 16, 20, 24, 32, 40, and 48 while the subjects are in the treatment phase of the study. Phone calls will be made to the participants at weeks 6, 28, 36 and 44 to monitor safety, compliance with study medication, and concurrent medications. There is an acceptable window +/- 1 day for visits at week 2, and 4, and a window of +/- 3 days for all other visits.

On the evening prior to the clinic visit at Week 2, study coordinators will instruct subjects by phone call to withhold their morning dose until they come to the clinic. This clinic visit will be scheduled around a subject's silymarin dosing such that prior to the end of the clinic visit, coordinators will witness the subject's ingestion of their dose and will then have a blood sample drawn between 30 minutes to 1 hour after dosing for the estimation of silymarin steady-state peak and trough plasma concentrations.

The following procedures will be performed at the study visits:

|                                |                                                                                 |
|--------------------------------|---------------------------------------------------------------------------------|
| Interim Medical History        |                                                                                 |
| Symptom-directed Physical Exam | Vital signs and weight at each visit; physical exam every 3 months or as needed |
| Adverse Event Assessment       | Each visit                                                                      |

|                                            |                                                                                                                                                                          |
|--------------------------------------------|--------------------------------------------------------------------------------------------------------------------------------------------------------------------------|
| Concurrent Medication Assessment           | Each visit                                                                                                                                                               |
| CBC/Differential                           | Each visit                                                                                                                                                               |
| Chemistry                                  | Each visit; ALT, AST, AlkPO4, total bilirubin, direct bilirubin, albumin, BUN, creatinine, glucose.
Week 12, 24, and 48 only: fasting triglycerides, glucose, insulin |
| Pregnancy Test                             | Urine, each visit                                                                                                                                                        |
| TSH                                        | Weeks 24 and 48                                                                                                                                                          |
| PTor INR                                   | Weeks 24 and 48                                                                                                                                                          |
| Silymarin level                            | Weeks 2, 4, 12, 16, 24, 32, 40, 48                                                                                                                                       |
| EKG                                        | Week 12                                                                                                                                                                  |
| Sample Storage                             | 20ml serum, 20ml whole blood, 10ml plasma, 24ml urine each visit from week 2 to week 24 and then week 48 (fasting at weeks 12, 24, and 48)                               |
| Pharmacokinetic Sample                     | Each visit according to assigned schedule or random sample                                                                                                               |
| Liver biopsy and CBC, ALT, AST, HOMAr      | Week 48 (or end of treatment)                                                                                                                                            |
| Adverse Event Assessment for Mental Health | Each visit                                                                                                                                                               |
| Questionnaires                             | Weeks 4, 12, 24, 48: SF-36, CLDQ, CES-D, ASE                                                                                                                             |
| Adherence Monitoring and Counseling        | Each visit
Monitoring by dose counts and review of diary entries                                                                                                      |

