## Silymarin

Milk Thistle, *silybum marianum*, has been used in both the treatment and prevention of liver diseases for over 2000 years. Silymarin, the active compound, consists of different flavonolignans including silibinin, isosilybin, silydianin, and silychristin. Among them, silibinin is the most biologically active compound, which makes up 50% of silymarin. The benefits of silymarin stem from its ability to function as a free radical scavenger and to stabilize plasma membranes. As free radical injury is often implicated in liver disease, silymarin has long been used in the treatment and prevention of hepatic disease.

Standardized extracts of milk thistle generally contain 70-80% silymarin, however, it is not regulated by the FDA. Pharmacokinetic studies estimate the bioavailability at 23-47%. Peak plasma concentrations are reached within approximately 2 hours, and range between 200 and 1400ug/L. The elimination half life is approximately 6 hours in healthy volunteers. The majority of ingested silymarin undergoes enterohepatic circulation and 20-40% of the ingested dose is recovered in the bile as both glucuronide and sulfate conjugates. Bile levels of silymarin peak within 2 to 9 hours and excretion continues for 24 hours. A much smaller amount, 2-5%, is excreted in the urine while an even smaller amount is excreted unchanged in stool. Silymarin has poor bioavailability; however, studies have shown that combination with phosphatidylcholine can increase biliary concentrations by as much as 3-11%. Pharmacokinetic studies have also been performed in cirrhotic patients. Compared to healthy volunteers ingesting an equivalent dose of silymarin, the time to maximum concentration was increased in cirrhotic patients.

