To balance the need to achieve the highest exposures possible and thus have the greatest chance of achieving efficacy for NASH patients, with the concern for patient safety, 700 mg three times daily was selected as the highest dose in NASH patients but will employ an early pharmacokinetic monitoring plan for  $\Sigma$  Free silymarin steady-state plasma concentrations (see Section 3.4.4) in addition to our safety assessments. Comparison of  $\Sigma$  Free silymarin plasma concentrations achieved after 2 weeks of chronic dosing with the peak plasma concentrations and associated adverse events reported by Flaig et al will make it possible to anticipate the need for greater vigilance for elevations in liver enzymes and bilirubin with the continuous chronic administration of 700 mg silymarin. Dose reductions or discontinuations for elevated liver enzymes and bilirubin are included in the routine safety procedures (see section 3.4.1).

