#### Pharmacokinetic Safety Monitoring

Blood samples will be collected and processed at each site and then shipped to the NIDDK repository. Aliquots needed for PK testing will be shipped to the central analytical lab at UNC. .Treatment week 2 samples from the first 6 patients receiving the highest dose (700 mg three times per day) will be used for bioanalysis to determine the range of  $\Sigma$  Free silymarin concentrations. Depending on the results, the determination of testing blood samples obtained from subsequent subjects will be made.

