### **Data and Safety Monitoring Board**

The DSMB members were appointed by the NCCAM and NIDDK. It consists of 5 members who have no financial, scientific, or other conflict of interest with the study. The DSMB acts as advisors to the NCCAM and NIDDK to monitor participant safety and study progress. The initial responsibility of the DSMB is to review the protocols and approve initiation of the study. Other responsibilities include reviewing informed consent documents; reviewing, commenting and approving the data and safety monitoring plan; assessing data quality, completeness, and timeliness; and evaluating recruitment and retention; monitoring risk versus benefit; consider factors external to the study when relevant information becomes available.

The DSMB will receive all MedWatch forms (FDA Form 3500A) submitted by the clinical centers for serious adverse events.

In the case of a serious adverse event requiring expedited reporting, the Data Coordinating Center will immediately notify [name] at the NCCAM, holder of the IND, the NCCAM and NIDDK Project Scientists, and the DSMB. For the purposes of this study, reports of all deaths will be expedited, regardless of whether they are considered to be unexpected or related to study drug.

In accordance with IND safety reporting regulations, [name], assisted by the Data Coordinating Center, will provide reports of serious adverse events requiring expedited reporting to the appropriate drug review division of the FDA and all participating investigators in writing within 15 calendar days of notification. Reports of serious, unexpected adverse events to the FDA will initially be conducted by telephone or fax within the required time frame (7 calendar days of notification by the clinical centers for telephone and fax safety reports). Following telephone/fax notification, written reports will be sent to the FDA.

The clinical centers are to report serious adverse events to the Data Coordinating Center within 24 hours of knowledge of the event so that notification can be provided as soon as possible following discovery of the event for reasons of patient safety. The clinical center PIs will be responsible for obtaining all information required to complete the adverse event report.

The DSMB will also review appropriate laboratory data annually.

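### The week-2 silymarin sample cannot give a trough and is likely to read below the peak it is compared with; separately, the DSMB's yearly laboratory review needs reconciling with its other review schedules.

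*Protocol*

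**What the plan says.** **Week-2 sample.** Section 4.3 (Study visit procedures) tells coordinators to "instruct subjects by phone call to withhold their morning dose until they come to the clinic". Staff watch the dose being taken and "then have a blood sample drawn between 30 minutes to 1 hour after dosing for the estimation of silymarin steady-state peak and trough" plasma concentrations. No pre-dose sample is specified there.

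**Stated kinetics.** The background section on silymarin says "Peak plasma concentrations are reached within approximately 2 hours" and "The elimination half life is approximately 6 hours in healthy volunteers". In the PK sub-study (Section 4.3.1, Sampling Design), visits at weeks 4, 16, 24 and 40 use a trough, a 1-2 h and a 2-4 h sample.

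**What the sample is for.** The dose-selection text in Section 1.0 reports non-linear free silymarin exposure. It cites an outside Phase I study in which free levels above 10-12 ug/ml went with transaminase and bilirubin rises. It says that comparing week-2 levels with that study's peak levels "will make it possible to anticipate the need for greater vigilance for elevations in liver enzymes and bilirubin". Section 3.4.4 (Pharmacokinetic Safety Monitoring) draws on week-2 "samples from the first 6 patients receiving the highest dose", and their results decide whether later subjects' samples are tested.

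**DSMB.** The review table in Section 7.5 gives adverse events quarterly, serious adverse events as they occur and laboratory data yearly. The text adds: "The DSMB will also review appropriate laboratory data annually". The Stopping rules paragraph leaves the frequency of DSMB safety review for the DSMB to determine.

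**The concern.** The week-2 sample is given two jobs. As a trough it fails by definition, because it is taken after a dose. As a peak it is doubtful, because the latest permitted draw (1 h) comes before the time by which the Protocol says the peak is reached. The reference value is a peak, so a pre-peak sample can only match it or fall short, and any error makes exposure at 700 mg look lower than it is. The dose-selection text itself says that free exposure at 700 mg may be substantially higher than anything seen in Phase I, and this sample is its early check on that.

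The DSMB matter is separate but concerns the same hazard. A moderate shift in liver tests in one arm shows up in tabulated laboratory data by arm. Sites are masked and see individual patients; only the DSMB closed report carries data by arm. On a yearly cycle, a patient treated for 48-50 weeks can start and finish between two laboratory reviews.

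**Working it through.** **1. Windows side by side.**

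| Item | Time after dose |
|---|---|
| Week-2 safety sample (4.3) | 0.5-1 h |
| Stated peak (background) | within about 2 h |
| PK sub-study, on treatment | pre-dose, 1-2 h, 2-4 h |
| PK sub-study, first dose only (Schedule 1) | 0-1 h, 1-3 h, 3-6 h |

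The week-2 window touches the 1-2 h window only at its end point and contains no pre-dose time.

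**2. Share of peak captured.** The Protocol gives no figure to reproduce, so a model is needed. Assumptions: one compartment, first-order absorption, dosing every 8 h, steady state at week 2, and 2 h taken as the single-dose peak time.

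- ke = ln 2 / half-life. For 6 h: 0.1155 per h.
- ka solves ln(ka/ke)/(ka - ke) = 2 h. This gives 1.342 per h.
- Steady state: C(t) is proportional to exp(-ke t)/(1 - exp(-8 ke)) - exp(-ka t)/(1 - exp(-8 ka)). Here 1 - exp(-8 ke) = 0.603, and the second denominator is practically 1.

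| Time | C(t), relative units | Share of peak |
|---|---|---|
| 0 h (trough) | 1.658 - 1.000 = 0.658 | 52% |
| 0.5 h | 1.565 - 0.511 = 1.054 | 84% |
| 1 h | 1.477 - 0.261 = 1.216 | 96% |
| 1.59 h (steady-state peak) | 1.380 - 0.118 = 1.262 | 100% |

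**3. Sensitivity (share of peak at 0.5 h and at 1 h).**

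| Case | 0.5 h | 1 h |
|---|---|---|
| Peak 2 h, half-life 6 h, every 8 h | 84% | 96% |
| Same, but 12 h since the last dose (late visit) | 78% | 94% |
| Peak 2 h, half-life 2 h, every 8 h | 66% | 89% |
| Peak 1 h, half-life 6 h, every 8 h | 96% | 100% |

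On the first row, a true peak of 10 ug/ml would read 8.4 to 9.6; on the third, 6.6 to 8.9.

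**4. Error if read as a trough.** With a 6 h half-life: 1.054/0.658 = 1.6-fold at 0.5 h and 1.216/0.658 = 1.85-fold at 1 h. With a 2 h half-life the trough is 22% of peak, giving 66/22 = 3.0-fold and 89/22 = 4.0-fold. The range is about 1.6 to 4.

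**5. Distance to the level of concern.** The highest free peaks quoted from Phase I are 1.77 ug/ml (560 mg, NAFLD) and 2.71 ug/ml (700 mg, HCV). 10/1.77 = 5.6 and 10/2.71 = 3.7.

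**6. The existing windows on the same model (2 h, 6 h, steady state).** The 1-2 h window reads 96-100% of peak and the 2-4 h window 82-99%.

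**7. DSMB statements.** The yearly laboratory interval (up to 12 months) is about as long as treatment (48-50 weeks). Two places in Section 7.5 fix it at yearly, while the Stopping rules paragraph leaves the frequency of safety review open.

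**The case against.** **The under-read is not proven.** The 2 h figure is an upper limit from background literature, not a measured time to peak for free silymarin in this population. The Phase I tables in Appendix 1 are not in the text available. If the peak comes at 1 h, a 1 h draw loses nothing. This stands, and it limits the claim to likely.

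**A pre-dose tube may be intended.** The visit table lists both a silymarin level and a pharmacokinetic sample at week 2, the morning dose is withheld, and Appendix 5 is not shown. This is plausible. But Section 4.3 assigns both peak and trough to the one draw it describes, so the wording needs correcting either way.

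**The Protocol does sample at 0-1 h elsewhere.** It does, but only after the first dose and as one of three windows, not as a stand-alone steady-state peak.

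**The check is not the main protection.** A reader might infer that the 700 mg dose depends on this sample as a go/no-go gate. The text does not say so. The check is additional to the other safety assessments, no trigger value is set, and liver tests are done at every treatment visit with severity-graded dose guidance.

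**The size is modest.** A reader might take the single-dose case with a 2 h half-life, where a 0.5 h draw reads about 54% of peak and 10 ug/ml would appear as 5.4. That case does not apply: week 2 is steady state and the stated half-life is 6 h.

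**The DSMB is not without liver data for a year.** Adverse events are defined to include abnormal laboratory findings and reach the DSMB quarterly, and serious events go as they occur. This stands. What remains is the systematic laboratory data: patients enter with AST or ALT above 40 IU/L, so a moderate further rise may not be recorded as an event.

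**Conclusion.** The point holds in a limited form. It is certain that one draw 30-60 minutes after a dose cannot estimate a trough, and that its window ends before the stated time to peak and does not match the on-treatment windows of the PK sub-study. It is likely, not established, that the comparison with outside peak levels reads low: by 4-16% on the Protocol's own figures at steady state, by 11-34% with a 2 h half-life, and by little or nothing if free silymarin peaks by 1 h. These sizes rest on the one-compartment assumption.

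The documents do not support the stronger inference that this error would by itself hide a dangerous level. The highest quoted Phase I free peaks lie 3.7- to 5.6-fold below 10 ug/ml. The Protocol's own warning of non-linearity makes the true level at 700 mg uncertain, which is a reason to time the sample properly.

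On the DSMB, the defect is an unreconciled schedule (yearly in two places, undecided in a third) and a yearly interval for systematic laboratory data that is about as long as treatment. It is not an absence of liver safety information.

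**What to change.** - **Week-2 visit.** Reconcile Section 4.3 with the background time to peak, the dose-selection text and the PK sub-study schedule. For the peak, use a post-dose window the Protocol already has. On the stated figures 1-2 h captures most of the peak, and it still contains a peak that falls at 1 h. For the trough, specify a pre-dose tube at the same visit, since the morning dose is already withheld.
- **DSMB.** Reconcile the yearly laboratory entries in Section 7.5 with the open frequency under Stopping rules. Add ALT, AST and bilirubin by arm to the closed part of the existing quarterly report.
- **Cost.** A slightly longer week-2 visit, one extra tube, and one extra table in a report already produced. Sample size, randomization and the efficacy analysis are unaffected.

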## Compliance Monitoring

Compliance will be assessed at the clinical sites by dose count and review of diary entries. In addition, weight/BMI determinations will be made during the study; because of the rigors associated with diet, exercise, and lifestyle consumption restrictions.

### 4.3.1 Pharmacokinetic study

Specific goals of the study pharmacokinetic analysis will include 1) confirming estimates of PK parameters obtained during phase I, in which only a small number of NAFLD patients were enrolled, 2) a comparison with the HCV population, 3) identifying the sources and magnitude of intersubject pharmacokinetic variability on the basis of covariates, 4) observing changes in metabolite kinetics over time, and 5) potentially linking safety and outcome measures to pharmacokinetic profiles. The specific analyses are outlined below in section 6.4.

## Subjects

The PK sub-study will provide samples according to the limited sampling strategy described below and will be used to develop a more robust population PK model and will also provide for an evaluation of the extent of intra-subject variability influencing covariates under investigation. All patients enrolled in the main study will be eligible to participate in the PK sub-study until the PK sub-study groups are filled. Of the 120 subjects enrolled in the main study, the first 30 who provide consent for the PK sub-study will be enrolled in the sub-study, 10 subjects per dose group.

## **Replacement dropouts**

The PK sub-study is using this limited subset of subjects to "predict" PK of the study population as a whole. For this reason participants who drop out the PK study will be replaced to successfully fill each dose group.

## **Sampling Design**

A limited sampling strategy will be employed in which a total of 54-60 ml (9-10 samples x 6 ml/sample) of blood will be drawn per patient for quantifying silymarin isomers. Sampling time windows have been selected to optimize PK information from a sparse sampling schedule based on our preliminary model. The 10 subjects in each dose group will be randomly assigned by the Data Coordinating Center to either Schedule 1 or 2 which will require additional PK sampling at 3 or 4 of the clinic study visits; 5 of these subjects will be sampled on Weeks 0, 24, and 48, while the other 5 subjects will be sampled on Weeks 4, 16, 40. Actual sample collection times will be recorded on the case report forms and be utilized in the subsequent analyses.

Sequential blood samples will be obtained from each subject on the same day according to the sampling schedule into which the subject is assigned.

### **Phase II NASH Trial**

|             |                                          |                                                               |
|-------------|------------------------------------------|---------------------------------------------------------------|
| Schedule 1: | First Dose:                              | 0-1 hours, 1-3 hours, 3-6 hours                               |
|             | Week 24:                                 | 0 hour (trough), 1-2 hours, 2-4 hours                         |
|             | Last dose (Day before follow-up Biopsy): | 0 hour (trough), 4-6 hours                                    |
|             | Day of follow-up biopsy:                 | 1 to 2 samples between 18-24 hours following last draw above* |
| Schedule 2: | Week 4:                                  | 0 hour (trough), 1-2 hours, 2-4 hours                         |
|             | Week 16:                                 | 0 hour (trough), 1-2 hours, 2-4 hours                         |
|             | Week 40:                                 | 0 hour (trough), 1-2 hours, 2-4 hours                         |

At the time of a scheduled study visit, which can be any time during the day, 6 ml blood samples will be obtained from all other study subjects not participating in the PK sub-study. Study coordinators will record the time of the most recent dose from subject report and record the time of sample collection. The inclusion of this sampling scheme will be used to further develop a robust population PK model and will provide for an evaluation of the extent of inter-subject variability influencing the covariates under investigation.

Blood will be collected for silymarin (Legalon®) and silymarin metabolite concentration (silibinin A and B, isosilibinin A and B, silicristin, and silidianin) at baseline and treatment weeks 2, 4, 12, 16, 24, 32, 40, and 48. Special attention will be paid to recording in source documents accurate sample collection times and timing of previous silymarin dose. Serum concentrations of free and total silymarin isomers will be quantified using LC/MS. Determination of the total fraction will be accomplished after hydrolysis with glucuronidase/arylsulfatase. The extent of phase 2 metabolism will be estimated from the quantitation of the amount of conjugated silymarin

---

\* Time of visit relative to administration of last dose. If close to 18 hrs at time of visit then also collect a 22-24 hrs timepoint depending on length of stay. If 22-24 hrs at time of visit then only 1 draw is needed. Prefer two draws in this window in order to determine the terminal half-life of the drug. The draws need to be at least 2 hrs apart.

isomers that will be calculated as the difference between the total and free fractions for each isomer.

